
### Data analysis

All data will be aggregated and analyzed. Quantitative data will be downloaded from a secure Canadian server to SPSS for data cleaning and analysis [42]. Data cleaning measures may include recoding into categorical variables and comparing and recoding free-text responses where appropriate. Descriptive statistics and estimation are the recommended focus of pilot/feasibility trials [43, 44]. Descriptive statistics (e.g., frequencies and measures of variation and spread) will be calculated to describe the study groups. Analyses by outcome measure are presented in Table 3. Analyses will be conducted based on intention-to-treat.

Initial data will be collected to perform a sample size calculation for a full-scale trial [43]. Estimation for knowledge and decision regret outcomes will focus on calculating confidence intervals of different widths to illustrate strength of preliminary evidence [43, 44]. Confidence intervals for the difference of means (paired) will be presented for both potential effectiveness outcome measures to account for repeated measures [45]. The confidence interval for the difference of means from time 1 to time 2 for both groups will be calculated to examine initial change scores and the difference of means from time 2 to time 3 for both groups will be calculated to examine sustained change score. Confidence interval widths for both initial and sustained change measures will be set at 99, 95, 90, 85, 80, and 75% and presented together alongside a minimum clinically important difference (MCID) in a graph [46]. If each confidence interval crosses both 0 and the MCID, this is inconclusive evidence of effect; however, if each confidence interval both excludes 0 and crosses the MCID, there is evidence of a potentially clinically important difference. A confidence interval that is above or equal to the MCID indicates that at this level there is a clinically meaningful difference between the groups.

Qualitative data will be de-identified during verbatim transcription. Prior to analysis, transcripts will be checked with the audio files for accuracy. Qualitative data will be managed and analyzed using NVivo data management software [47]. Qualitative outcomes will be analyzed using thematic analysis by breaking interview text into small units for a detailed, nuanced account of the data [48–50]. This iterative process will be concurrent to data collection [37]. Thematic analysis will be guided by the hybrid approach of inductive and deductive coding and theme development described by Fereday and Muir-Cochrane [51]. Deductive coding of the interview transcripts will be done first using the semi-structured interview guide as a framework; smaller units of data that emerge inductively will be coded for increased granularity and specificity. To ensure analytic rigor, field notes will be collected during the data collection and analysis process and coded alongside interview data [48, 52, 53].

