**Methods:**

A single-site, parallel-arm, pilot randomized trial will be conducted. The trial will employ quantitative and qualitative methods to evaluate feasibility objectives in key scientific, process, management, and resource domains. Parents seeking care for a child with AGE in the emergency department (ED) over a 6-month period will be randomized to receive the whiteboard animation video or a sham control video. Quantitative data will be collected electronically in the ED and at home (4–10 days post-ED visit). Qualitative data will be collected via semi-structured interviews with experimental condition participants after quantitative data collection. Data will be collected to perform a sample size calculation for a full-scale trial. Scientific outcomes will include parental knowledge, decision regret, and health utilization, and estimation for these outcomes will use confidence intervals (CI) of different widths to illustrate strength of preliminary evidence. CIs will be presented alongside minimum clinically important differences (MCIDs) calculated using two methods: (1) data driven and (2) patient perspective. Descriptive statistics will be calculated to describe process, management, and resource domain outcomes. Qualitative thematic analysis will be conducted to describe additional process, management, and resource outcomes in the experimental group. Analyses will be performed using intention-to-treat.

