The following data will be collected over the course of this study:Pre-intervention questionnaire (baseline, see Additional file 1): Participants will complete a pre-intervention questionnaire that includes demographics, knowledge questionnaire, and Decision Regret Scale within the iCare Adventure platform on the iPad.**Participants will then be randomized to view the study intervention or the standard care intervention within the iCare Adventure platform on the iPad. This process will be seamless for the participants.Post-intervention questionnaire 1 (immediate, see Additional file 2): After viewing the intervention, participants will complete the knowledge questionnaire and Decision Regret Scale a second time. In addition, participants will complete two items assessing their own performance on the knowledge questionnaire and Decision Regret Scale and one item regarding the perceived value and benefit of the KT tool. They will also be asked if they would like a video link emailed to them. At the end of this questionnaire, parents will be informed that the post-intervention questionnaire 2 will be emailed to them 4 days after this ED visit for completion at their earliest convenience. Experimental intervention group parents will be asked about participation in a qualitative focus group at this time.Post-intervention questionnaire 2 (4–14 days post-ED, see Additional file 3): Participants will be emailed a secure link on day 4 post-ED discharge to complete the knowledge questionnaire and Decision Regret Scale a third time, two items assessing their own performance on the knowledge questionnaire and Decision Regret Scale, three items related to healthcare utilization, and three items related to the perceived value and benefit of the KT tool (if applicable). Reminders to complete post-intervention questionnaire 2 will be sent to those who have not completed the survey every third day (day 7, 10, 13) to complete the survey by day 14 post ED-discharge. Previous research has demonstrated that 82% of AGE cases are resolved in 3 days or less and 14 days [40] represents the outer limit for pediatric AGE resolution [41].Post-intervention semi-structured interview (sub-sample of experimental group, see Additional file 4): Participants in the experimental group indicating willingness to participate in an in-depth, semi-structured, qualitative interview will be contacted via telephone after completion of post-intervention questionnaire 2. Up to three phone calls will be made to establish interview date/time. Qualitative interviews will focus on satisfaction with iCare Adventure platform, perceived benefit and value of the KT intervention, and willingness to participate in future, similar research.

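### The time 2 to time 3 paired estimate, as stated, uses only parents who return questionnaire 2, and the questionnaire 2 window differs between Abstract and Methods

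*Protocol article*

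**What the plan says.** **Analysis basis.** The Abstract (Methods) says "Analyses will be performed using intention-to-treat", and the Data analysis section repeats it: "Analyses will be conducted based on intention-to-treat". The article does not define the term further.

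**Estimator.** Data analysis fixes the method for knowledge and decision regret: "Confidence intervals for the difference of means (paired) will be presented for both potential effectiveness outcome measures to account for repeated measures". Two changes are named. For the initial change, "The confidence interval for the difference of means from time 1 to time 2 for both groups will be calculated"; for the second, "the difference of means from time 2 to time 3 for both groups will be calculated to examine sustained change score".

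**Source of the scores.** Times 1 and 2 are both collected on the iPad in the emergency department. Time 3 comes from questionnaire 2, reached through a link emailed on day 4 (Data collection). Table 3 lists the percentage of drop-outs at questionnaire 2 as a process outcome. No imputation, mixed model or complete-case rule is named.

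**Window.** The Abstract says "Quantitative data will be collected electronically in the ED and at home (4–10 days post-ED visit"). The Data collection section says "Post-intervention questionnaire 2 (4–14 days post-ED, see Additional file 3"), with reminders on days 7, 10 and 13 and completion by day 14.

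**The concern.** A paired difference from time 2 to time 3 exists only for a parent who has both scores. With no step to fill in missing time 3 scores, parents who do not answer the email leave the sustained-change estimate entirely, including the time 1 and time 2 scores they have already given. Parents who reply to a follow-up email about a video may well differ in knowledge or regret from those who do not. The average change among responders then need not be the average change among all randomised parents, which is what a reader of the intention-to-treat label would expect.

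The sustained-change intervals are to be plotted against the MCID and read as preliminary evidence, so a shifted mean could move that reading. The window matters for a related reason. Several feasibility results depend on how long parents are followed for questionnaire 2, and the article gives two lengths.

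**Working it through.** The plan states no drop-out rate, SD, correlation or expected change, so there is no figure of its own to reproduce. The check has three parts.

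**1. Which estimates depend on questionnaire 2**

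| Estimate | Scores needed | Affected by loss at questionnaire 2? |
|---|---|---|
| Time 1 to time 2 | both in the emergency department | no |
| Time 2 to time 3 | emergency department and emailed questionnaire 2 | yes |

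**2. Possible size of the bias (every input is assumed)**

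Inputs: knowledge score SD 1.5 at times 2 and 3, correlation ρ = 0.6, true mean change -0.50 item, 60% reply, and log-odds of reply rising by 0 to 0.6 per item of time 2 score.

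For a parent with time 2 score X and mean μ, the expected change is -0.50 + (ρ - 1)(X - μ) = -0.50 - 0.4(X - μ). The responder-only mean change is therefore -0.50 - 0.4 × (mean time 2 score of responders minus μ).

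| Slope of log-odds per item | Responders' time 2 mean minus μ | Responder-only mean change | Shift |
|---|---|---|---|
| 0 | 0 | -0.50 | 0 |
| 0.3 | 0.26 | -0.50 - 0.4 × 0.26 = -0.60 | -0.10 |
| 0.6 | 0.46 | -0.50 - 0.4 × 0.46 = -0.68 | -0.18 |

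The differences of 0.26 and 0.46 were obtained by numerical integration, with the intercept set so that 60% reply. A simulation of 2,000,000 pairs gave -0.598 and -0.682. Using the observed time 2 score in a regression recovered -0.50 in each case.

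The SD of the change among all parents is √(2 × 1.5² × (1 - 0.6)) = √1.8 = 1.34. Among responders it is 1.34 at slope 0.3 and 1.32 at slope 0.6, so the SD is little affected.

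More generally, with a share d not replying, the responder-only mean is shifted by d times the gap in mean change between responders and non-responders. For d from 10% to 50% and an assumed gap of 1 point, the shift is 0.1 to 0.5 points.

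**3. The window**

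Contacts fall on day 4 + 3k: days 4, 7, 10 and 13. Days 4, 7 and 10 lie inside both windows. The day 13 reminder, and any answer on days 11 to 14, lies outside 4–10 and inside 4–14. Only the Methods window fits the reminder schedule and the day 14 end point. The following results depend on it:

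- drop-out at questionnaire 2 and the percentage completing it (Table 3, process domain);
- average days to completion (Table 3, resource domain);
- post-visit healthcare utilization, which is asked in questionnaire 2;
- the time 2 to time 3 estimates.

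**The case against.** A reader might infer that the plan contradicts itself by declaring intention-to-treat and then analysing completers. The documents do not prove that. Intention-to-treat can mean analysis by allocated group, and a paired change within allocated groups is compatible with it. Imputation before pairing is neither adopted nor ruled out, and a fuller protocol or analysis plan that is not shown may deal with missing scores. This part of the objection stands. What remains is that the article does not leave the method open: it names an estimator that, as written, drops non-responders, when a better one is readily available.

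The size is also open to challenge. All inputs are assumed, and the shift is 0.10 to 0.18 points on a 0–8 scale. It is a shift within one arm, so if reply depends on score in the same way in both arms, much of it would cancel in a comparison between arms. The plan's paired intervals, however, are computed for each group, where nothing cancels. A further inference, that a distorted SD would spoil the sample size of the full-scale trial, is not supported: the SD barely moves, and the article does not say which outcome or time point will supply it.

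On the window, neither statement is a rule for accepting or discarding answers; both describe when data are collected. The Methods text is consistent within itself, so this is a small correction. It is still a plain conflict between two figures in one document, which condensing a protocol into an article does not explain.

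**Conclusion.** The point holds as a better-method recommendation together with one inconsistency to reconcile. The stated paired estimator for time 2 to time 3 can use only parents who return questionnaire 2, and its mean is biased if reply is related to earlier scores. On the assumed inputs the bias is 0.10 to 0.18 items, or 20% to 36% of an assumed true change of -0.50 (0.10/0.50 and 0.18/0.50). It is zero if reply is unrelated to score. The true size cannot be known before the pilot reports its reply rate. The time 1 to time 2 estimate is untouched by loss at questionnaire 2. A breach of intention-to-treat is not established; the label is undefined for missing time 3 scores.

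The window conflict, 4–10 against 4–14 days, is explicit and rests on no assumption.

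**What to change.** Estimate the changes in knowledge and decision regret with a linear mixed model (time by arm, repeated measures within parent) on all randomised parents, in the arm to which they were allocated. The time 1 and time 2 scores of non-responders then contribute. The planned set of interval widths and the MCID display can stay as they are. Report the paired responders' result as a sensitivity analysis, and say in one sentence what intention-to-treat means when questionnaire 2 is missing.

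Give one collection window for questionnaire 2 in both the Abstract and Methods. The reminder schedule and the day 14 end point fit 4–14 days, so the Abstract figure is the one that needs attention.

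The cost is a few sentences, one corrected figure and a little more analysis work; the model can be fitted in SPSS, which the plan already names. The remaining weakness is that the model removes the bias only if reply depends on observed scores. It does not protect against non-response driven by the unseen time 3 score.

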### Randomization

Blocked randomization with randomly chosen block sizes will be used to ensure equal distribution of participants to the experimental and sham intervention study arms [31]. The blocked randomization sequence will be computer generated. Following sequence generation, the randomization sequence will be entered into a confidential module on the electronic platform. Once the sequence is entered, the randomization module will only be accessible using a confidential password. The randomization sequence will be kept confidential. It will be inaccessible to data collectors/outcome assessors and to the study participants.

After completing the pre-intervention questionnaire, including demographic information and baseline outcome data, on the electronic data collection platform, individual parents/caregivers will automatically be randomized to one of the study conditions (i.e., experimental intervention or sham control) based on the randomization sequence. This process will be seamless to participants. After viewing the study condition materials, participants will be automatically directed to post-intervention questionnaire 1. At study completion, all participants will receive a thank you email with links to both videos shown in the study.

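### Knowledge and regret are estimated from paired change scores but read as group differences; a between-arm estimate adjusted for the pre-randomisation score would be a cheap gain

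*Protocol article*

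**What the plan says.** Both effectiveness scores are taken before allocation. The Data collection section says of the baseline step: "Participants will complete a pre-intervention questionnaire that includes demographics, knowledge questionnaire, and Decision Regret Scale". The Randomization section places automatic allocation after that step: "After completing the pre-intervention questionnaire, including demographic information and baseline outcome data, on the electronic data collection platform".

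The Data analysis section then fixes the estimator: "Confidence intervals for the difference of means (paired) will be presented for both potential effectiveness outcome measures to account for repeated measures". It defines two contrasts. The initial one is: "The confidence interval for the difference of means from time 1 to time 2 for both groups will be calculated to examine initial change scores". The second is described as "the difference of means from time 2 to time 3 for both groups will be calculated to examine sustained change score". Six confidence levels apply to both: "Confidence interval widths for both initial and sustained change measures will be set at 99, 95, 90, 85, 80, and 75" per cent. The interpretation rule is between-group: an interval at or above the minimum clinically important difference (MCID) "indicates that at this level there is a clinically meaningful difference between the groups".

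On later use of the data, the same section says: "Initial data will be collected to perform a sample size calculation for a full-scale trial". It does not name the SD, the correlation or the analysis that would feed that calculation. Neither this section nor Table 3 mentions a model with the baseline score as a covariate.

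**The concern.** The article does more than leave the analysis to another document. It states the estimator, the contrasts, the confidence levels and the reading rule. Within that stated method, a baseline measured before randomisation is used less well than it could be.

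- **Initial change (time 1 to 2).** Baseline is used by subtraction, which fixes its slope at 1. With equal SDs the best-fitting slope is the correlation rho, which is below 1, so subtraction adds noise to a comparison of the arms.
- **Sustained change (time 2 to 3).** Baseline is not used, and the starting value is itself affected by the video. If the between-arm effect is e2 at time 2 and e3 at time 3, a between-arm contrast of this change estimates e3 - e2. A benefit that is fully retained would give 0. This contrast shows whether an effect fades. It does not show the effect at follow-up.

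The pilot expresses the strength of its preliminary evidence through intervals and is meant to inform the size of the full-scale trial. The between-arm estimate and its SD are therefore the quantities it most needs to deliver.

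**Working it through.** The article states no sample size, SD, correlation or effect size, so there is no figure of its own to reproduce. The values of rho, the SDs and the effect size below are assumptions. Equal allocation comes from the Randomization section.

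**1. Variance per parent for a between-arm contrast.** Let s1 be the baseline SD, s2 the follow-up SD and rho their correlation.

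- Change score: s1² + s2² - 2·rho·s1·s2
- Baseline-adjusted (ANCOVA): s2²·(1 - rho²)
- Change minus ANCOVA: (s1 - rho·s2)², which is never negative

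With s1 = s2 = 1 these become 2(1 - rho) and 1 - rho². Their ratio, ANCOVA to change, is (1 + rho)/2. The width ratio is its square root, and the sample-size inflation is 2/(1 + rho).

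| rho | Change variance | ANCOVA variance | Variance ratio | Width ratio | Narrower by | Inflation of N |
|---|---|---|---|---|---|---|
| 0.3 | 1.40 | 0.91 | 0.65 | 0.81 | 19% | 1.54 |
| 0.5 | 1.00 | 0.75 | 0.75 | 0.87 | 13% | 1.33 |
| 0.7 | 0.60 | 0.51 | 0.85 | 0.92 | 8% | 1.18 |
| 0.9 | 0.20 | 0.19 | 0.95 | 0.97 | 3% | 1.05 |

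The width ratio is the same at all six confidence levels, apart from a negligible difference in degrees of freedom.

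**2. What the inflation means for a full-scale trial (illustration).** Take an assumed effect of 0.3 SD, two-sided 5% and 90% power. Total N = 4·V·(1.96 + 1.28)²/0.3², which is about 467·V. At rho 0.5 that is 467 × 1.00 = 467 on the change-score SD, against 467 × 0.75 = 350 on the adjusted SD. At rho 0.3 it is 654 against 425, and at rho 0.7 it is 280 against 238.

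**3. Sensitivity to unequal SDs.** The gain disappears when s1 = rho·s2, for example s1 = 0.7, s2 = 1, rho = 0.7. It grows if follow-up scores bunch near the ceiling of the 0–8 knowledge score. With s1 = 1, s2 = 0.7 and rho = 0.5, the change variance is 1 + 0.49 - 0.70 = 0.79 and the ANCOVA variance is 0.49 × 0.75 = 0.37. The interval is then about 32% narrower with adjustment.

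**4. The intervals as worded.** A paired interval within one arm of n parents has variance 2(1 - rho)/n with unit SDs. The ANCOVA difference between two arms of n has variance 2(1 - rho²)/n. At rho 0.5 and n = 50 the standard errors are √(1.00/50) = 0.141 within one arm, √(2 × 0.75/50) = 0.173 for ANCOVA, and √(2 × 1.00/50) = 0.200 for the between-arm change. A simulation of 1,000 runs gave 0.140, 0.173 and 0.199. The within-arm interval is the narrowest, but it does not compare the arms. With no treatment effect and an assumed shift of 0.3 SD common to both arms, the within-arm 95% interval lay wholly above 0 in 57% of runs.

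**The case against.** The strongest reply is that the intervals as worded are within each arm, and these are not too wide. Step 4 shows they are narrower than ANCOVA intervals. A reader might infer that all six intervals are wider than the data allow, but the text does not support that. The loss arises only once the arms are compared on change. What remains is that the article reads the intervals between groups without naming an estimate that compares the groups.

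A reader might also infer that the full-scale sample size will rest on an inflated SD. The article does not say which SD will be used. A change-score SD is the right input if the later trial analyses change. Parent-level scores at all three times will exist, so the residual SD can be computed later. This reply stands, and the inflation factors are conditional.

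Third, the size depends on an unstated correlation. Times 1 and 2 fall in one waiting-room session around a 3-minute video, so rho could be high and the gain only about 3%. That also stands.

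Fourth, a randomised comparison of change scores is unbiased, so chance baseline imbalance affects precision and conditional balance and does not make the estimate biased. The article also says that hypothesis testing is not its focus, which makes power a weak yardstick. Both are correct, and the case here rests on interval width.

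Finally, change scores fit the patient-perspective MCID, which uses parents' ratings of their own change. That is a good reason to keep the paired changes as description. It is not a reason to omit an adjusted between-arm estimate.

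**Conclusion.** The point holds as a free or cheap improvement in precision and in what is estimated. The plan reads its intervals as group differences but names only paired changes, with baseline subtracted in one contrast and absent from the other. For a between-arm comparison of time 1 to 2 change, baseline adjustment would narrow intervals by about 19% to 3% as rho goes from 0.3 to 0.9, assuming equal SDs. The matching sample-size factor is 1.54 to 1.05, and it applies only if a trial analysed with adjustment is sized on the change-score SD. These percentages do not describe the time 2 to 3 contrast, where the issue is that it does not estimate the effect at follow-up. The documents do not show that the planned estimates are biased or invalid.

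**What to change.** In the Data analysis section, specify for each outcome the experimental-minus-sham difference at time 2, and separately at time 3, from a linear model (ANCOVA) of that score on arm and the parent's own time 1 score. Use time 1 as the covariate at both times, because time 2 is measured after the video. Draw the six intervals from these estimates and set them against the MCID. Keep the paired within-arm changes as descriptive results. Report the residual SD and the time 1–2 and time 1–3 correlations, so that the full-scale trial can be sized for whichever analysis it adopts.

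The cost is a few sentences and one regression per outcome and time point in SPSS, with no new data. The downside is one extra estimated slope and an assumption of approximate linearity in the baseline score.

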To address the research-practice gap in pediatric AGE and provide parents with a reliable, research-based information resource, our research team developed a 3-min whiteboard animation video using patient-oriented research methods [25]. Whiteboard animation videos are short, hand-drawn, and narrated videos optimized for online streaming. Video content was drawn from knowledge synthesis results of treatment and management strategies for pediatric AGE [1]. The video storyline was developed from a qualitative study (*n* = 15) that gathered and synthesized stories from parents/caregivers of children with vomiting and diarrhea who visited an ED for healthcare [8]. Video prototypes were reviewed, and a final version approved by pediatric emergency clinicians, research nurses, and parents. The video depicts a family with a sick child trying to determine whether medical attention is required. The family recalls an information sheet given to them at a hospital when their child was ill with the same symptoms at an earlier time. The family assesses their child using the information sheet and determines to monitor and manage the child’s illness at home until symptoms resolve. The family describes worsening symptoms that would require them to take their child to the emergency department. Artists, including a script writer, animators, and voice actor, were contracted to work with the research team to ensure high-quality video production.

Rigorous evaluation of the effectiveness of the whiteboard animation video is a critical next step. Given some uncertainty regarding the most appropriate methods for evaluating the effectiveness of KT tools for parents [26], including best outcome measures and parameters for sample size calculations, we have chosen to first undertake a pilot trial [27–29]. We are also interested in exploring the feasibility of using an electronic platform to assist with recruitment, intervention delivery, and data collection. The study objectives are listed in Table 1 according to four key pilot trial domains [27].

**Table 1 Tab1:** Study objectives

Pilot trial domains	Study objectives
Scientific domain	• To estimate the potential effectiveness of a digital knowledge translation tool for parents/caregivers about pediatric AGE. Effectiveness outcomes include knowledge, decision regret, and post-ED healthcare utilization.

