## Methods

This is a parallel-arm, randomized, pilot trial. Convenience sampling will be used to recruit parents/caregivers seeking care for a child with vomiting and diarrhea in the ED and randomize them to receive the intervention of interest (i.e., whiteboard animation video) or a sham control condition (i.e., standard video of similar length). Data will be collected using quantitative and qualitative methods over a 6-month period. This protocol has been registered on clinicaltrails.gov (NCT03234777) and has obtained ethics approval from the University of Alberta Health Research Ethics Board and operational approval from the provincial health authority.

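### The evidence rule speaks of a difference between the groups, but the only intervals specified are paired changes within each group

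*Protocol article*

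**What the plan says.** The Methods section states the design: "This is a parallel-arm, randomized, pilot trial". The control is a sham video of similar length. Table 1 gives the scientific objective: "To estimate the potential effectiveness of a digital knowledge translation tool for parents/caregivers about pediatric AGE".

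The Data analysis section specifies the estimator for knowledge and decision regret: "Confidence intervals for the difference of means (paired) will be presented for both potential effectiveness outcome measures to account for repeated measures". It then names two contrasts:

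- Initial change: "The confidence interval for the difference of means from time 1 to time 2 for both groups will be calculated".
- Sustained change: "the difference of means from time 2 to time 3 for both groups will be calculated to examine sustained change score".

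The confidence levels "will be set at 99, 95, 90, 85, 80, and 75" percent, and the intervals are plotted with the MCID. Two readings favour the video. Under the first, "if each confidence interval both excludes 0 and crosses the MCID, there is evidence of a potentially clinically important difference". Under the second, an interval at or above the MCID "indicates that at this level there is a clinically meaningful difference between the groups". The same section says the data will feed a sample size calculation for the full-scale trial.

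**The concern.** A paired interval compares parents with themselves at two times. The two arms hold different, unmatched parents, so a paired interval cannot be a contrast of the arms. The rule therefore draws a between-group conclusion from a within-group quantity.

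This matters because a within-arm change contains everything that happens to both arms. From time 1 to time 2 the obvious component is retest gain: the same questionnaire is repeated straight after a 3-minute video. From time 2 to time 3 parents have also had standard ED care and, at the physician's discretion, the hospital's information sheet. The sham video can remove these components only if the arms are contrasted.

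At stake are the pilot's statement on potential effectiveness and the effect carried into the full-scale sample size calculation.

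**Working it through.** **Text.** No between-arm interval, in change or in follow-up score, is named in the Data analysis section, in Table 3 or in the abstract. Both the specified estimator (paired, to handle repeated measures) and the specified contrasts (time 1 to 2, time 2 to 3) are within-person. Only the concluding sentence of the rule is between-group.

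**Arithmetic.** The protocol fixes no sample size, SD or MCID value, so there is no figure of its own to reproduce. The following illustrates the knowledge score (0 to 8), time 1 to time 2.

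Assumed inputs: n = 60 per arm, SD of change s = 1.5, MCID m = 0.5, gain g = 0.8 in both arms, video effect 0.

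1. Within-arm standard error: s/√n = 1.5/√60 = 0.194.
2. Probability that the 99% paired interval in the experimental arm excludes 0: noncentral t with 59 df, noncentrality g/SE = 0.8/0.194 = 4.13, critical value 2.66. Result: 0.92. The six intervals are nested, so whenever the 99% interval excludes 0, all six do.
3. Probability that the 75% interval lies above the MCID: noncentrality (g − m)/SE = 0.3/0.194 = 1.55, critical value 1.16. Result: 0.65.
4. Range for step 3:

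| MCID | gain 0.5 | gain 1.0 |
|---|---|---|
| 0.5 | 0.125 | 0.92 |
| 0.75 | 0.01 | 0.55 |

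5. Varying n from 30 to 100 and s from 1.5 to 2.0, still with no video effect, the chance that the experimental arm's 95% paired interval excludes 0 is 10% to 38% for a common gain of 0.25, 26% to 91% for 0.5, and 75% to over 99% for 1.0.

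**Between-arm contrast.** The common gain cancels. The standard error of the difference in mean change is s√(2/n) = 1.5 × √(2/60) = 0.274, so the within-arm standard error is 0.194/0.274 = 0.71 of it. With no video effect this interval excludes 0 at its nominal rate whatever the gain: 1% at the 99% level, 5% at 95%, 25% at 75%.

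**One worked outcome.** Assume n = 50 per arm, s = 1.5, an observed gain of 1.0 in both arms, and an MCID equal to the standard error of measurement with SD 1.6 and reliability 0.7: 1.6 × √0.3 = 0.88. The within-arm intervals run from 0.43 to 1.57 (99%) down to 0.75 to 1.25 (75%). All six exclude 0 and contain 0.88, so the rule reports a potentially clinically important difference. The between-arm 95% interval is −0.60 to 0.60.

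**The case against.** The strongest reply is that the text is condensed. The phrase about both groups, together with the conclusion about a difference between them, could be shorthand for comparing the paired changes across arms. That reading is possible, but it does not fit an estimator specified as paired. If it was intended, the sentence still has to be corrected. The documents support saying that no between-arm interval is named; they do not show that the authors mean to avoid one.

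A second reply is that this is a pilot without hypothesis testing. That is true, and no test is asked for here. The plan nevertheless sets its own evidence rule and aims to estimate effectiveness, so the rule should act on the right quantity.

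A third reply is that the sham arm's intervals will be shown too, so a common gain would be visible. This stands as mitigation: a careful reader could derive the between-arm difference and its standard error from the two arms. The stated rule does not do so.

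The illustration is also open to criticism. It covers knowledge from time 1 to 2 only, and its main case assumes a retest gain larger than the MCID. With gain 0.5 and MCID 0.75 the probability falls to 0.01.

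Three stronger inferences are tempting, and the documents do not support them:

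- *The full-scale trial would inherit a wrong SD.* The SD of within-person change in each arm is a valid input for sizing a two-arm comparison of change.
- *Regression to the mean inflates the change.* The eligibility criteria in Table 2 do not select on knowledge or regret score, so no systematic shift of the group mean is expected.
- *ED care inflates the immediate change.* The video is viewed before the physician consultation and time 2 follows at once, so ED care can matter only by time 3.

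**Conclusion.** The contradiction holds on the text alone: paired within-group intervals are specified, and a between-group conclusion is drawn from them. As written, the rule can credit the video with a change that both arms share. The size depends on quantities the protocol does not give. Under the assumed values in the main case (60 per arm, SD 1.5, MCID 0.5, common gain 0.8), the chance of a false reading is about 0.92 for all six intervals excluding 0, and 0.65 for the 75% interval lying above the MCID. The latter ranges from 0.01 to 0.92 over the gains and MCIDs tried.

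The error lies in the analysis wording. Randomisation, the sham control and the data collection are unaffected, and the data allow the correct contrast. It should be corrected before analysis, because the pilot's effectiveness statement and the effect used for the full-scale trial rest on it.

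**What to change.** Apply the six-level interval display and the 0/MCID rule to the experimental-minus-sham difference in change from baseline, once at time 2 and once at time 3, for both outcomes. Keep the within-arm changes, including time 2 to time 3, as description. Take the effect for the full-scale sample size from this between-arm contrast, with an SD that matches the chosen analysis.

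A plain between-arm difference in change repairs the defect. Adjusting for the time 1 score, by ANCOVA or a mixed model over the three times, is preferable because that score is already collected. With equal variances at the two times and correlation ρ between them, the adjusted variance is (1 + ρ)/2 of the change-score variance: 0.65, 0.75 and 0.85 for assumed ρ of 0.3, 0.5 and 0.7.

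The cost is a change of wording and no new data. The downside is wider intervals: with equal arms and no adjustment, the standard error is √2, or about 1.41, times the within-arm one. The MCID methods in Table 3 rest on the standard error of measurement and on participants' ratings of their own change, so the revised text should also say how that threshold is applied to a difference between arms.
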